### Ethical Considerations

The Ethics Committee of the TAU (approval no. 246, date of approval: April 23, 2018) approved the study protocol. In addition, the study protocol followed the SPIRIT (Standard Protocol Items: Recommendations for Interventional Trials) guidelines (Checklist 1). This study has been registered with the University Hospital Medical Information Network (UMIN ID: 000043725). All participants with CNSLBP are required to understand and approve the purpose of the study and sign a written informed consent form. All participant data were anonymized using coded identifiers. Data were stored in password-protected databases and locked storage facilities for 10 years. Participants received one free acupuncture treatment after completion of follow-up questionnaires as compensation for participation.

## Results

Recruitment started in October 2018. Data collection was temporarily suspended from April 2020 to September 2022 due to COVID-19 restrictions that prohibited in-person clinical research activities. Recruitment resumed thereafter, and data collection was completed in March 2025. There were no significant deviations from the original trial registration.

## Discussion

### Principal Findings

This study evaluates the short-term specific efficacy of penetrating acupuncture using both objective (FRP) and subjective (pain intensity) measurements in patients with CNSLBP. To achieve this, we compared 3 interventions, including a penetrating needle, a skin-touch needle, and a no-touch placebo needle that is physiologically inert, to better understand the key component factor of acupuncture. We hypothesized that FRP would be restored alongside improvements in subjective pain in the penetrating acupuncture group compared to the skin-touch and the no-touch placebo groups. This study aims to provide a better understanding of the specific versus nonspecific therapeutic components of acupuncture.

CNSLBP lasting more than 3 months with no apparent cause represents a large portion of patients with LBP and imposes a significant economic burden on many countries [1,2,4]. No definitive effective treatment for CNSLBP has yet been established. Acupuncture has been recommended as an empirically effective treatment for LBP based on the efficacy of acupuncture reported in unblinded and single-blinded studies [22,23]; however, the scientific basis of these findings is weak. The results of these studies may be biased due to a lack of acupuncturist and/or participant blinding [26,34,35]. Blinding acupuncturists, which is the most challenging problem in acupuncture research, as well as blinding participants, has the potential to increase study rigor.

In studies of CNSLBP using sham acupuncture as a control, the immediate effect of genuine acupuncture was no better than sham acupuncture for pain reduction [26]. Studies using these shams underestimate the effectiveness of acupuncture [35] because these sham techniques are physiologically active [67,68]. In this study, we solve this problem by using no-touch placebo acupuncture needles that do not stimulate the skin. The results of this study will begin to provide definitive results regarding the efficacy of acupuncture and sham acupuncture for the treatment of CNSLBP.

This study also uses FRP, which is an index of LBP [11,13,46]. FRP is recorded using sEMG, an objective measure, that reduces the potential to introduce bias into the study. Testing the efficacy of acupuncture by combining changes in self-reported and objective indicators enhances the rigor of the study results. Additionally, the study examines the immediate physiological effects after a single acupuncture session. Although acupuncture in clinical settings usually involves multiple sessions, evaluating the immediate response offers valuable mechanistic insight into the specific physiological effects of needle penetration. Understanding these short-term responses is an important first step toward clarifying the biological mechanisms behind acupuncture treatment.

By combining a rigorous double-blind design with both objective physiological measures and subjective clinical outcomes, this study aims to clarify the specific contribution of needle penetration to acupuncture efficacy in patients with CNSLBP.

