### Inclusion Criteria and Exclusion Criteria

#### Inclusion Criteria

A physician from TAU Medical Clinic and a research assistant from TAU Acupuncture Clinic identify eligible participants based on the following criteria: (1) are aged 18-65 years, (2) have a diagnosis of CNSLBP, and (3) have other physical treatments such as physical therapy, massage, or take medications for CNSLBP one week before they are assigned to the treatment group and for the duration of the study.

Concomitant physical therapy, massage, or stable medication use is permitted for ethical and pragmatic reasons, reflecting real-world management of CNSLBP. Participants are instructed not to initiate new treatments during the study period. Randomization is expected to distribute co-interventions evenly across groups, thereby mitigating systematic confounding while preserving external validity.

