### Intervention

#### Acupuncture Needles

Three types of double-blind needles (Confidence Co, Ltd; Figure 2) were used in this study: (1) genuine penetrating needles that pierced the skin and underlying tissue (Figure 2A; 5‐ to 20-mm depth depending on location and penetrating group), (2) skin-touch needles with a blunt tip that contacted the skin without penetration (Figure 2B; approximately 2 mm compression; skin-touch group), and (3) no-touch inert placebo needles that were designed so the tip did not contact the skin, providing a physiologically inert control condition (Figure 2C; no-touch group). From external appearance, all 3 needle types are indistinguishable. Therefore, it is not possible for participants and acupuncturists to make a judgment regarding the type of needle being used by how it looks. Also, there is silicone inside the inner guide tube that wraps around the needle and offsets the resistance to the needle insertion force [54]. This enables blinding of the participant and acupuncturist, as they cannot feel the needle type. The structure of the double-blind needles has been described in detail elsewhere [38-45,54-57]. The diameter of all 3 types of double-blind needles in this study was 0.20 mm. The penetrating needles were inserted to a depth of 5-20 mm (Table 1), depending on the anatomical location of where each needle was placed. The needles were sterilized using ethylene oxide gas prior to packaging.

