### Treatment Procedure

Before treatment, the acupuncturist read the following script to each participant, “You are going to be randomly assigned to one of three groups: the penetrating needle group, the skin-touch needle group, or the no-touch needle group. The penetrating needle group is the treatment using real acupuncture needles that penetrate the skin, the skin-touch needle group is the treatment using skin-touch acupuncture needles that touch the skin but do not penetrate, and the no-touch needle group is the treatment with no-touch acupuncture needles with tips that do not touch the skin.” All participants were given one free real acupuncture treatment upon the return of their surveys one week later. Individuals not meeting study inclusion criteria were also offered free acupuncture.

Next, the acupuncturist asked the participant to point out the most severe stiffness or pain in the lumbar, gluteal, and posterior thigh regions. Participants then lay supine on a treatment table.

Before each needle application, the acupuncturist massaged each acupoint with the fingertip of the index finger of the nondominant hand in a circular motion for 2 seconds. This insertion technique is a commonly practiced method in Japanese-style acupuncture. The assistant peeled off the adhesive paper covering the bottom of the pedestal of each needle device, covered the needle with an outer guide tube, and handed it to the acupuncturist. Then, the acupuncturist placed the needle device on the acupoint, which was held in place by the adhesive. The acupuncturist stabilized the needle device with the nondominant hand and tapped the top of the needle handle, which protruded from the outer guide tube, 5-7 times using the index finger of the dominant hand [66].

After needle tapping-in, the acupuncturist removed the outer guide tube and inserted the needle further to its targeted depth by rotating it clockwise and counterclockwise using an alternating twirling technique [38-45,54,66]. This process was repeated until all needles were inserted. The needles were retained for 15 minutes.

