After 15 minutes, the acupuncturist withdrew each needle to its initial position using an alternating twirling technique to remove them [38-45,54,66]. The needle was then stored in an opaque envelope to prevent the group allocation from being revealed. After all needles were removed, the research assistant checked for bleeding from each needled insertion site and wiped the blood away with a cotton ball and/or applied pressure if needed. The acupuncturist again massaged the area where the needle was inserted.

Then, the acupuncturist assessed the participant for back pain. If the participant had no pain, the treatment was complete. If the participant still had pain, the hardest indurations and the most tender areas in the lumbar erector spinae, quadratus lumborum, gluteus medius, and biceps femoris were treated using a Sparrow Pecking technique (rapidly inserting and withdrawing the needle tip within a 2 mm amplitude) using another needle from the same set of needles randomly assigned to the participant [13].

After the acupuncture treatment was complete, participants rated the intensity of their LBP on a 100 mm VAS. Participants then completed the MASS. The participants then guessed whether the treatment was “penetrating,” “skin-touch,” “no-touch,” or “cannot identify the needle type.” They reported their confidence level in their guesses on a 100 mm VAS ranging from 0 (no confidence) to 100 (full confidence) [37-43,52,63]. The acupuncturists were also asked to guess the needle type and rated their confidence in their guess. The sEMG of the lower back was recorded using the same procedure as before the intervention. One week after treatment, participants brought the completed questionnaires (intensity of LBP on VAS, RMDQ, and JOABPEQ) back to the Acupuncture Clinic. At that time, a research assistant offered them a free acupuncture treatment with regular acupuncture needles.

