### Strengths

The strength of our study lies in its rigorous methodological design, which addresses several critical challenges in acupuncture research. By using a triple-arm, double-blind design—consisting of a penetrating needle, a skin-touch placebo, and a physiologically inactive placebo—we effectively controlled for nonspecific therapeutic effects. Furthermore, the inclusion of objective physiological indicators (FRP) alongside subjective measurements significantly enhances the clinical rigor and reliability of our findings.

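### The no-touch arm is described as a physiologically inert, non-stimulating control, but the shared procedure gives it massage, adhesive contact and tapping; only the needle tip can be called inert

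*Protocol article*

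**What the plan says.** Three places in the protocol article claim inertness beyond the needle tip, or can be read that way.

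- Methods, Acupuncture Needles: "no-touch inert placebo needles that were designed so the tip did not contact the skin, providing a physiologically inert control condition". The claim is made for the condition.
- Discussion, Principal Findings: after stating that sham techniques are active and make acupuncture look less effective than it is, the article says "we solve this problem by using no-touch placebo acupuncture needles that do not stimulate the skin".
- Discussion, Strengths: the third arm is "a physiologically inactive placebo—we effectively controlled for nonspecific therapeutic effects".

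The Introduction and the Conclusions make a narrower statement, that the no-touch needle is inert.

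The Treatment Procedure is a single procedure for all participants. Before needling, "the acupuncturist massaged each acupoint with the fingertip of the index finger of the nondominant hand in a circular motion for 2 seconds". The device is then fixed to the acupoint by adhesive, steadied by hand, tapped 5-7 times and twirled. After 15 minutes the needles are withdrawn, and then: "The acupuncturist again massaged the area where the needle was inserted". The post-treatment VAS and sEMG follow later in the same visit. No step is restricted to particular arms. The Limitations section mentions none of these shared components.

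**The concern.** The article argues that earlier trials could not show a benefit of acupuncture because their controls were themselves active, and that this trial removes the problem. That argument needs a control condition that does not stimulate the skin. The procedure describes something else: a needle whose tip does not reach the skin, delivered inside a hands-on routine that does stimulate it.

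Interpretation is what is at stake. Principal Findings promises results on the efficacy of acupuncture and of sham acupuncture. If the no-touch arm is taken as inert, a null result would be read as acupuncture being no better than an inert placebo, and the before-after change in that arm would be read as pure placebo response. The delivered condition supports neither reading.

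**Working it through.** No figure in the documents bears on whether the arm is inert, so the check is a comparison of sections, followed by a count of exposure.

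**1. What each section claims.** The Introduction and Conclusions refer to the needle, and nothing in the Treatment Procedure contradicts them: the tip is designed not to touch the skin. Acupuncture Needles goes further with "providing a physiologically inert control condition". The Principal Findings sentence has needles as its grammatical subject but offers them as the cure for active shams. Strengths can be read either way.

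**2. What the no-touch arm receives, in the order written (Treatment Procedure).**
- circular fingertip massage at each acupoint, 2 seconds
- adhesive pedestal on the skin, device held in place by hand
- 5-7 taps on the handle, then twirling
- 15 minutes with the device in place
- withdrawal, then a second massage of unstated length
- pain check, with further needling from the assigned set if pain remains
- VAS, sensation scale, needle guess and confidence, then sEMG

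The closing massage cannot be confined to sites that were really penetrated, because the acupuncturist does not know which needle was used.

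**3. The article's own standard.** The Introduction relays the argument that the earlier single-blind placebo needle, which presses the skin, is not physiologically inert. If blunt pressure at a point counts as active, fingertip massage at the same point cannot be assumed inactive. The inclusion criteria also name massage among physical treatments for the condition ("Concomitant physical therapy, massage, or stable medication use is permitted"), although a 2-second motion per point need not be equivalent to that.

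**4. Where the contact falls.** Under Baseline Assessment the sEMG electrodes lie beside L4 and L5 and on the hamstrings. In Table 1, BL25 and BL26 lie at the L4 and L5 levels, and BL37 lies between two hamstring muscles. The massage is therefore on or near the muscles that supply the objective primary outcome.

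**5. Amount of contact.** Table 1 lists 18 acupoints, and Randomization gives 40 needles per set. The article does not say whether every point is needled on both sides, so both cases are shown as assumptions:

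| Assumption | Sites | Massage before needling | Taps |
|---|---|---|---|
| All points, both sides | 18 × 2 = 36 | 36 × 2 s = 72 s | 36 × 5 = 180 to 36 × 7 = 252 |
| All points, one side | 18 | 18 × 2 s = 36 s | 18 × 5 = 90 to 18 × 7 = 126 |

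The two-sided case fits a set of 40 (40 − 36 = 4 left over), but this does not prove it. These counts describe exposure only and imply no effect on VAS or sEMG.

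**6. Consequence for the contrasts.** Write the post-treatment response in an arm as shared handling (H) plus the needle's contribution (N). If the two are additive, penetrating minus no-touch is (H + N_pen) − (H + N_no) = N_pen − N_no, and H cancels. The same holds for skin-touch minus no-touch. The within-arm change for no-touch is H + N_no plus placebo response and time effects, and H does not cancel there. If H and N are not additive, for example because handling already lowers pain and leaves less room to improve, the contrast could shrink. The documents give nothing from which to size this.

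**The case against.** The strongest reply is that the design does what a placebo control should do. Massage, pedestal and tapping are given alike in all arms by blinded acupuncturists, and holding the handling constant is how the effect of the needle is isolated. The Discussion states the aim as the part that needle penetration plays, and penetrating versus no-touch serves that aim. Most of the inertness statements are about the needle, and they stand. The massage is brief, and no effect of it is documented. All of this is correct, and it limits the point to description and interpretation.

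A reader might infer more than the documents support.

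- **That there is no inert placebo in the trial, or that the control is invalid.** The inertness of the tip is not contradicted, and the randomized comparison is intact.
- **That the shared handling biases the comparison.** Common handling does not do so by itself. Attenuation would need a floor effect or an interaction, which is possible but unquantified.
- **That skin-touch versus no-touch cannot show whether a touching sham is active.** The two arms differ only in the needle, so a difference would show an effect of tip contact (about 2 mm of compression) over the common background.
- **That measuring before the closing massage would solve the problem.** In the written order that massage precedes the pain check and any further needling, so treatment would not yet be complete. The opening massage, adhesive and tapping would also remain, and data collection ended in March 2025.

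The reply does not rescue the wording that extends inertness to the condition, or the claim that the active-sham problem is solved.

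**Conclusion.** The point holds as a matter of description and of what may be concluded. Acupuncture Needles, Principal Findings and, on its natural reading, Strengths attribute to the no-touch arm a property that the Treatment Procedure does not deliver. The needle tip may be inert. The control condition is not shown to be, and by the article's own criterion it cannot be assumed to be. The between-arm contrasts remain valid estimates of what tip contact or penetration adds to a shared hands-on procedure.

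The size of any effect of the handling on VAS or sEMG cannot be derived from the documents. The exposure counts depend on how many points were needled and on how many sides. The conclusion rests on reading the Treatment Procedure as applying to all arms, which is how it is written.

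**What to change.** 1. Reconcile Acupuncture Needles, Principal Findings and Strengths with the Treatment Procedure. Describe the arm as a needle without tip contact, delivered within massage, adhesive contact and tapping common to all arms. Keep the word inert for the needle tip.
2. Add the shared handling to Limitations, noting that it precedes both post-treatment primary measurements and that its effect on them is unknown.
3. In the results report, restrict the conclusions to the added effect of tip contact or penetration over the shared procedure. State that a null result does not show acupuncture to be equal to an inert placebo, and that the change within the no-touch arm is not a pure placebo response.

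This needs text changes only and leaves the data and the planned analysis untouched. The cost is a somewhat narrower claim than the one now made in the Discussion.

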### Strengths

The strength of our study lies in its rigorous methodological design, which addresses several critical challenges in acupuncture research. By using a triple-arm, double-blind design—consisting of a penetrating needle, a skin-touch placebo, and a physiologically inactive placebo—we effectively controlled for nonspecific therapeutic effects. Furthermore, the inclusion of objective physiological indicators (FRP) alongside subjective measurements significantly enhances the clinical rigor and reliability of our findings.

### Limitations

Despite these strengths, several limitations should be noted. First, since the primary objective was to evaluate immediate posttreatment effects following a single intervention, our findings may not be extrapolated to the long-term clinical efficacy of repeated acupuncture sessions. However, identifying these immediate physiological changes is a crucial first step in elucidating the underlying mechanisms of acupuncture for CNSLBP. Second, the design of the double-blind needles prevented practitioners from perceiving de-qi, as the device is specifically engineered to blind the practitioner to the depth of insertion. While some traditional perspectives emphasize the importance of de-qi, its definitive relationship with specific acupuncture efficacy remains inconclusive and warrants further rigorous investigation [69].

### Conclusions

This study has several distinctive methodological features, as outlined below:

This study is the first randomized double-blind (acupuncturist-participants) placebo-controlled trial to test the short-term effects of acupuncture on CNSLBP.This study uses a genuine penetrating needle and 2 placebo needles, a skin-touch needle and a no-touch needle that is physiologically inert, to better understand the key component of acupuncture.This study evaluates the effects of acupuncture on CNSLBP using both self-report measurement (pain intensity) and an objective measurement (activation of the erector spinae muscles using surface electromyography).
